## Method and Design

### Setting

The study will be conducted at the University Medical Center Hamburg-Eppendorf (UKE), Germany, as part of the Collaborative Research Centre (CRC) SFB 289. In addition to its own study-specific outcomes, the trial also contributes to centrally coordinated assessments defined by the CRC. These centrally collected measures serve overarching research aims and are implemented uniformly across all participating sub-projects (for a preregistration, see: OSF Registries | SFB289 - Central Project NeuroImaging). These centrally coordinated assessments include neuroimaging to examine structural and functional brain connectivity prior to the experimental procedures, as well as the collection of salivary biomarkers such as cortisol awakening response and alpha-amylase activity. In addition, participants complete a standardised set of psychological questionnaires. These data will contribute to cross-project analyses aimed at identifying individual predictors of expectancy-related effects, particularly in relation to stress responsiveness, affective disposition and pain sensitivity.^30^ The study is expected to begin in July 2025, with patient recruitment due to conclude by July 2026. The final follow-up assessments will end in July 2027.

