#### Admission and Enrolment of the patients

The preoperative consultation is performed by the treating physician at the Helios ENDO-Clinic in Hamburg, a leading high-volume arthroplasty centre with high expertise. Based on the patient’s symptoms, imaging and established THA guidelines, surgery will be recommended as the appropriate treatment. Following the diagnosis of OA and the planning of primary THA, the practitioner will screen the patient for study eligibility using a checklist. Patient meeting the inclusion criteria will receive detailed information about the study. If they consent to participate, they will be enrolled and subsequently randomised to their respective intervention groups. All participants will receive oral and written information and must provide written informed consent before enrolment. A sample of the patient information and consent form is available in the online supplemental materials.

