### Blinding and randomisation

The study researcher responsible for analysing the primary outcomes will remain blinded to group allocation by working with a concealed group variable (group variable with hidden label). Since the intervention involves direct delivery by the study physician, the physician must be aware of group assignment to conduct the informed consent process using augmented communication where applicable. To minimise researcher bias, only trained study physicians deliver the augmented consultations (aDOC), while standard consultations (TAU) are provided by clinicians who are not involved in the intervention. Study staff administer the video separately after the physician’s visit, ensuring that consulting physicians remain unaware of whether a participant has received it. This design intentionally introduces a potential experimenter effect, allowing for the investigation of the impact of enhanced physician-patient interaction as part of the intervention itself (‘effects of augmented communication’). Blinding of the study researcher, who is unaware of the group allocation, is designed to minimise this risk as much as possible.

Participants will be randomly assigned to one of the four study groups using a block randomisation method to ensure balanced group sizes throughout the recruitment period. The block size will be kept constant at 20 and will not be disclosed to the physicians involved in recruitment. Allocation concealment will be achieved by using sealed, opaque and sequentially numbered envelopes. Each patient will draw one envelope on inclusion, thereby determining their group assignment by chance. This procedure ensures both randomisation integrity and transparency while minimising selection bias.

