## Sample size calculation

This RCT will include 200 patients undergoing THA due to hip OA. The sample size was determined through an a priori power analysis using G*Power designed to detect interaction effects in a repeated measures ANOVA for the primary outcome of pain intensity. Based on our previous work, we assumed a small to medium effect size of f=0.15 for interaction effects with α=0.05 and 1 - β=0.90, resulting in a required sample size of n=164 (4 groups).^8 10 29^

To account for potential exclusions or dropouts and to enable stratified randomisation by sex/gender into the four study arms while balancing the sex/gender of the patient featured in the video intervention, we aim to recruit a total of n=200 patients, with n=50 per group. Eligibility will be assessed consecutively for all patients scheduled for THA at the UKE (Location: Helios ENDO-Clinic, UKE).

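### The constant block size of 20 is printed in the protocol article, so someone following the consultations could know about 9% of aDOC/non-aDOC assignments in advance

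*Protocol article*

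**What the plan says.** The protocol article describes the allocation in its section Blinding and randomisation: "Participants will be randomly assigned to one of the four study groups using a block randomisation method to ensure balanced group sizes". It continues: "The block size will be kept constant at 20 and will not be disclosed to the physicians involved in recruitment". Concealment is by sealed, opaque, sequentially numbered envelopes, and the section presents the procedure as keeping selection bias small.

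The same section sets out who knows what:

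- **aDOC factor.** It is open to those who deliver it: "the physician must be aware of group assignment to conduct the informed consent process using augmented communication where applicable". Trained study physicians give the augmented consultation, and clinicians outside the intervention give the standard one.
- **Video factor.** Study staff show the video separately, "ensuring that consulting physicians remain unaware of whether a participant has received it".

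Other sections supply the setting. Under Admission and Enrolment, "the practitioner will screen the patient for study eligibility using a checklist", before consent and randomisation, and all surgery is at one clinic. The Setting section is written ahead of enrolment, with "patient recruitment due to conclude by July 2026". The Sample size section states that "we aim to recruit a total of n=200 patients, with n=50 per group". It adds that randomisation is to be stratified by sex/gender and that eligibility is assessed consecutively in all scheduled patients.

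**The concern.** Sealed envelopes hide what the next envelope contains. They do not stop anyone inferring it from what has already been opened. With a block of known and constant size, the remaining places are known once one type of assignment is used up. The plan accepts that knowing the size is a risk, since it keeps the size from recruiting physicians, but the article itself states it. Because the size never changes, a person who has found the block boundaries can stay in step from block to block.

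At stake is the comparison of patients with and without the augmented conversation on a self-reported pain outcome. Some exclusion criteria need judgement: severe mental illness, severe cognitive impairment, substance abuse. A screener who expects a particular assignment could, even unintentionally, apply them more or less strictly. Blinding the analyst acts after enrolment and does not address this.

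**Working it through.** **Inputs.** Block size 20, constant, and four groups (Blinding and randomisation); 200 patients, 50 per group (Sample size calculation). Assumed observer: knows the block size, sees all earlier aDOC/non-aDOC assignments, does not see video assignments, and is in step with the blocks.

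**1. The plan's own figures.** 200/20 = 10 blocks. Each block has 20/4 = 5 places per group, so 10 × 5 = 50 per group, as stated. Two of the four groups receive aDOC, so each block holds 2 × 5 = 10 aDOC and 10 non-aDOC places.

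**2. Places known for certain.** A place is certain once all 10 of the other type have gone, that is, when all the places left in the block are of one type. The probability that at least the last L places are of one type is

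P(L) = 2 × C(20−L, 10−L) / C(20, 10).

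This gives P(1) = 1.000, P(2) = 0.474, P(3) = 0.211, P(4) = 0.087. The sum over L = 1 to 10 is 20/11 = 1.82 certain places per completed block; a simulation of 200,000 blocks gave 1.817. Over 10 blocks: 10 × 1.82 = 18.2 of 200, or 9.1%. In 1 − 0.474 = 53% of blocks only the last place is certain.

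**3. The two places before the last.**

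- 19th place: 0.474 + 0.526 × 1/2 = 0.737.
- 18th place: 0.211 + 0.789 × 2/3 = 0.737.

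Each is guessed correctly 74% of the time.

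**4. Average guess rate.** Always guessing the type with more places left is correct for 10 + ½ × (2^20 / C(20, 10) − 1) = 10 + ½ × (1,048,576/184,756 − 1) = 12.34 of 20, or 61.7%, against 50% by chance.

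**5. Effect of stratification.** If blocks run within each sex, the observer must follow two sequences, with the same 1.82 certain places per completed block. If both strata fill whole blocks, there are still 10 blocks. If not, 9 blocks are completed (9 × 1.82 = 16.4 certain places) and 20 patients fall in two unfinished blocks.

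**6. Alternatives.** For a fixed block of size b, the certain share is 1/(b/2 + 1). Randomly varied sizes were assessed by simulating trials of 200 patients (two runs of 300 trials each). The observer knows the set of sizes but not their order, and updates on what has been seen.

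| Scheme | Certain, per 200 | At least 80% sure, per 200 | Average guess rate |
|---|---|---|---|
| Fixed 20 | 18.1-18.3 | 22.9-23.3 | 61.7% |
| Random among 12, 16, 20, 24, 28 | 0.5-0.8 | 3.9-4.8 | 61-62% |
| Random among 4, 8, 12 | 5.4-5.8 | not used here | 66% |

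Fixed small blocks would be worse than 20: the certain share is 33% at size 4 and 20% at size 8, against 9% at size 20.

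**The case against.** The best defence is that the route from predictable places to bias is long. A block of 20 is already large, and in about half of the blocks only the final place is determined. The count requires an observer who sees every earlier assignment, yet delivery is split between two sets of clinicians and the treating practitioner does the screening. One clinic does not mean one observer. Stratification by sex/gender makes the tracking harder. The article gives no publication date relative to enrolment, so reading by a recruiter during that period is an assumption. Consecutive assessment of all scheduled patients limits steering, and neither pain level nor ordinary anxiety is an exclusion criterion. All of this stands, and it keeps the point modest.

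Three stronger readings are tempting, and the documents do not support them:

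- **Physicians learn each patient's full group.** They do not. Consulting physicians are kept unaware of the video, so only the aDOC/non-aDOC split can be tracked.
- **A recruiter could put off enrolment to a more favourable place in the sequence.** No later preoperative visit is described. Randomisation and the first intervention fall on the same day, about 4 days before surgery. The route left is judgement at screening.
- **No analysis could deal with the resulting bias.** Too absolute. The Abstract compares changes in pain, and Table 1 records pain at T-4, so selection on baseline pain would be visible and partly accounted for. Selection on traits that were not recorded would not be.

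What the defence does not answer is that the stated safeguard is non-disclosure of a number that the same document discloses.

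**Conclusion.** The point holds as a cheap improvement with a modest benefit. A constant block size that appears in the protocol article cannot be relied on to stay unknown to recruiters, and the aDOC factor can be followed from who gives the consultation. Under the assumptions in the check, about 18 of 200 aDOC/non-aDOC assignments (9%) could be known before enrolment, including the last place of every completed block.

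The figure counts predictable places. It does not estimate bias in the pain outcome. A reader might infer that concealment has failed or that selection will occur. The documents show neither: they do not establish that any recruiter sees the full count, has read the article while enrolling, or would act on it. The weakness is that the size is constant and public, not that it is 20.

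**What to change.** For all unopened envelopes, replace the constant size with block sizes varied at random among multiples of 4, for example 12, 16, 20, 24 and 28, within each sex stratum if randomisation is stratified as the Sample size section says. Avoid a mix of small blocks only, which raises the average guess rate. Have the list generated and held by a person outside recruitment and intervention delivery, and do not publish the sizes until recruitment ends.

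The cost is refilling the remaining envelopes and one sentence of amendment. Group sizes may end slightly away from 50 each if the last block is incomplete. No extra patients or staff are needed. The gain is that certain assignments almost disappear; the average guess rate hardly changes.

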## Objectives and Outcomes

### Primary objective (subjective pain measure)

The primary objective of this study is to reduce postoperative pain by optimising preoperative treatment expectations. Pain will be assessed using a numerical rating scale (NRS 0–10) documented in a patient diary, and the Pain and State of Health Inventory (PHI). The PHI captures both pain intensity and the subjective experience over time, enabling a multidimensional evaluation of postoperative pain.

### Secondary objectives

#### Subjective outcome measures

The secondary objectives include the reduction of postoperative functional impairments and evaluating the overall pain area, including its localisation and spatial extent, by distinguishing between interoceptive pain (bone/hip area) and exteroceptive pain (wound/surface).^33 34^

In addition, the study will investigate dynamic changes in the formation of patients’ expectations over time. Furthermore, we aim to clarify the role of self-efficacy in shaping these expectations both before and after surgery. Expectations will be analysed in terms of both an outcome (change over time) and potential moderation of the treatment effects on postoperative outcomes, such as pain and functional recovery.

The functional status and pain related to hip conditions will be assessed with the Harris Hip Score.^35^ The Quality of Recovery-15 questionnaire^36^ will be used to measure the quality of recovery, while the PHI^37^ will be used to quantify the impact of negative mood and distress on quality of life during the acute postoperative period. Self-efficacy will be evaluated using a modified, validated questionnaire measuring patients’ confidence in performing functional activities aligned with the study’s outcomes.^38 39^ This questionnaire has been validated for the study’s purpose and has been tailored to the study’s functional outcome measures. In addition, a general questionnaire on self-efficacy for arthritis,^40^ including hip OA, will be used. Surgery-related treatment expectations will be assessed using the Stanford Expectations of Treatment Scale (SETS),^41^ while postoperative pain management expectations will be evaluated with the GEEE tool^42^ and NRS scales to assess treatment expectations. Postoperative sickness symptoms and perceived treatment efficacy will be analysed using diverse questionnaires such as the Quality of Recovery-15.^31^ Finally, patients will rate the perceived credibility, warmth and competence of the study physician with the scale developed by Fiske *et al*,^43^ based on the “Stereotype Content Model” (SCM) as well as a specially developed questionnaire and the CARE-D questionnaire.^44 45^

#### Exploratory measures

As part of an exploratory analysis of physiological response measures, blood samples will be collected repeatedly to quantify interleukin-6 (IL-6), C-reactive protein (CRP), erythrocyte sedimentation rate (ESR), and cortisol. These markers are well-established indicators of systemic inflammation and physiological stress and are considered relevant to recovery following orthopaedic surgery.^46^,^48^ Since psychological stress and negative expectations have been linked to elevated inflammatory responses, we aim to explore whether interventions designed to optimise treatment expectations can attenuate biological stress markers. The data will be analysed to explore inflammatory dynamics during both early and post-acute phases, with the aim of identifying potential associations between biological stress responses and subjective reports of pain and sickness symptoms.

The specific parameters assessed are outlined in table 1.

**Table 1 T1:** Outcome measures.

Domain	Measures	Timepoints	Method
Pain	Comparison Pain NRS	T-4, T3, daily during hospital stay	Survey, pain diary
	GCPS^49^	T-4a	Survey
	PDI^50^	T-4a, follow-up	Survey
	GEEE-Effekt^42^	Post T2-T3, follow-up	Survey
	SBI (PHI; Pain Health Inventory)	T-4a / T-4b, post T1-T3, follow-up	Survey
	DN4/DN2^51^	T-4/T1	Examiner / survey
Treatment Expectations	GEEE-Erwartung^42^	T-4a, T-4b	Survey
	SETS^41^	Pre: T-4a, T-4b; post: T2-T3, follow-up	Survey
	Behandlungserfolg PR-OP^8^	T-4a, T-4b, post T1-T2, follow-up	Survey
Mobility	Harris Hip Score^35^	During hospital stay follow-up	Physician examination survey
Patient Physician Relationship	CARE^45^	T-4b, T1	Survey
	Wärme u. Kompetenz^52^	T-4b, T1	Survey
Psychological Trait and State	STADI Trait^53^	T-4a	Survey
	STADI State^53^	T-4a, post T2, follow-up	Survey
	PSS^54^	T-4a; T4	Survey
	SSAS^55^	T-4a; T5	Survey
	FSS^56^	T-4a, post T1	Survey
Postoperative Recovery	QoR-15^36^	Post T1	Survey
	Medication Intake	Daily during hospital stay	Pain diary
Self-efficacy	ASES-D^40^	T-4a/ T-4b, post T1-T3, follow-up	Survey
Systemic inflammation	Laboratory parameter (IL-6, CRP, ESR)	T-4a, post T1, post T3, follow-up	Central clinical laboratory
Physiological stress	Laboratory parameter (cortisol)	T-4a, post T1, post T3, follow-up	Central clinical laboratory

ASES-D, Arthritis Self-Efficacy Scale German version; Behandlungserfolg PR-OP, Perceived Treatment Success Pre-/Post-Op; CARE, Consultation and Relational Empathy Measure; CRP, C-reactive Protein; DN4 / DN2, Douleur Neuropathique 4 / Douleur Neuropathique 2; ESR, Erythrocyte Sedimentation Rate; FSS, Fatigue Severity Scale; GCPS, Graded Chronic Pain Scale; GEEE-Effekt, Göttingen Questionnaire on Experience and Evaluation of Health Care Effect scale; GEEE-Erwartung, Göttingen Questionnaire on Experience and Evaluation of Health Care Expectation scale; Harris Hip Score, Harris Hip Score; IL-6, Interleukin-6; NRS, Numeric Rating Scale; PDI, Pain Disability Index; PSS, Perceived Stress Scale; QoR-15, Quality of Recovery-15; SBI (PHI), Surgical Behavior Inventory (Pain Health Inventory); SETS, Stanford Expectations of Treatment Scale; SSAS, Somatosensory Amplification Scale; STADI Trait / State, State-Trait Anxiety-Depression Inventory; T1, 1 day postoperative; T2, day of discharge; T3, 1-month follow-up; T4, 3-month follow-up; T5, 6-month follow-up; T-4b, 4 days preoperative, after the intervention; Timepoints: T-4a, 4 days preoperative, before the intervention; Wärme u. Kompetenz, Warmth and Competence Scale.

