## Abstract

**Introduction:**

Osteoarthritis (OA) commonly affects the ageing population, particularly the hip joint. Total hip arthroplasty (THA) is a frequent procedure that relieves pain and improves mobility, though some patients experience persistent postoperative pain. With rising numbers of THA, optimising perioperative care and pain management is crucial to address the growing clinical burden and improve patient outcomes. Positive treatment expectations have shown promise in enhancing outcomes, especially in pain management. This study implements two strategies to optimise the patient’s treatment expectations, comprising enhanced physician communication and digital social observational learning. We will examine their separate and combined effects on preoperative expectations, negative emotions, postoperative pain, inflammation and function during recovery up to 12 months postoperatively.

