### Study aims and questions

The aim of this study is to improve postoperative outcomes, particularly pain and functional disability, within the clinical context of pain management in patients undergoing THA. We will investigate the effects of physician communication and social observational learning on the dynamic changes in patients' treatment expectations and, consequently, on postoperative pain perception and functional impairments in patients undergoing THA.

The following are the key questions in this study:

Can augmented practitioner communication and/or a digital social observation learning intervention effectively optimise preoperative treatment expectations and emotional states in patients undergoing THA?Can preoperative expectation management, especially the combination of both strategies, result in improved postoperative health outcomes, especially in terms of pain and functional capacity?Do the effects of enhanced communication and social observational learning on expectations and on postoperative subjective and objective outcome dynamics combine in an additive or in a synergistic manner?Does expectation management enhance pain-related self-efficacy expectations, reduce preoperative anxiety and stress levels and impact postoperative recovery on subjective and physiological levels, including inflammatory markers?

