### Intervention and study groups

The intervention is delivered at two time points: 4 days before surgery (during the preoperative consultation) and on the first postoperative day. These timings are chosen to optimally shape and reinforce patient expectations.

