#### Augmented communication-based expectation manipulation (aDOC)

The intervention consists of a structured physician-patient conversation developed for this study, drawing on findings from placebo research and expectation-based interventions in pain and surgical outcomes. It targets both the cognitive dimension, by providing clear and understandable medical information about the procedure, postoperative course and expected recovery, and the emotional dimension, by expressing empathy, warmth, and reassurance.

Randomisation takes place at the baseline visit, approximately 4 days before surgery. On the same day, participants receive their assigned intervention. The physician conversation is during the preoperative visit and focuses on establishing realistic yet positive expectations, addressing potential patients concerns and supporting the patient’s sense of control. The postoperative session, on the first day after surgery, reinforces these expectations, encourages adaptive coping strategies and strengthens the therapeutic relationship.

The intervention is conceptually based on evidence demonstrating that the doctor-patient interaction itself can influence clinical outcomes. Previous studies have shown that positive expectations can reduce symptom intensity and analgesic use, and that the combination of physician warmth and competence produces the strongest effects on patient experience and symptom relief.^8 10 30 31^ The standardised approach ensures consistency while allowing flexibility to respond to individual patient needs.

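### No dedicated anxiety or stress measure is scheduled between the first intervention session and surgery, so the preoperative anxiety and stress components of key questions 1 and 4 cannot be estimated from the listed scales

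*Protocol article*

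**What the plan says.** Under Study aims and questions, key question 1 asks whether the interventions can "effectively optimise preoperative treatment expectations and emotional states in patients undergoing THA". Key question 4 asks, among other things, whether expectation management can "reduce preoperative anxiety and stress levels". The abstract's introduction likewise announces an examination of "separate and combined effects on preoperative expectations, negative emotions" and later outcomes.

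The section Intervention and study groups places the two sessions at "4 days before surgery (during the preoperative consultation) and on the first postoperative day". The aDOC section has randomisation at the baseline visit and adds: "On the same day, participants receive their assigned intervention".

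The legend to Table 1 splits the baseline visit in two. T-4a comes before the intervention, and the other half is "T-4b, 4 days preoperative, after the intervention". T1 to T5 all lie after surgery. In Table 1 the STADI State row reads "T-4a, post T2, follow-up". PSS is listed at T-4a and T4, and blood cortisol at T-4a, T1, T3 and follow-up.

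**The concern.** To show that an intervention changed a preoperative state, the state has to be measured after the intervention and before the operation. The plan has a time point for this and uses it for expectation, self-efficacy and physician-relationship scales, but not for its anxiety and stress measures.

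The first post-intervention anxiety score is taken at discharge. By then it also reflects the operation, postoperative pain, relief that surgery is over, and the second session on day 1. A group difference at that point is a legitimate postoperative result, but it does not answer a question about anxiety before surgery. Once a patient has gone to surgery, the missing value cannot be recovered by any later choice of analysis.

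**Working it through.** No power, alpha or sample-size figure bears on this point, so there is nothing to recompute. The check sets each Table 1 schedule against the time-point definitions in the table legend.

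**Step 1: which time points can show a preoperative effect?** The value must follow the first session and precede surgery. T-4a precedes the session. T1 (day 1 after surgery), T2 (discharge), T3 (1 month), T4 (3 months) and T5 (6 months) follow surgery. Only T-4b qualifies.

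**Step 2: which anxiety and stress measures are taken at T-4b?**

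| Measure | Before first session | At T-4b | First later value |
|---|---|---|---|
| STADI State | T-4a | none | T2, discharge |
| PSS | T-4a | none | T4, 3 months |
| Blood cortisol | T-4a | none | T1, day 1 after surgery |

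The count at T-4b is 0 of 3. The T-4a value precedes the intervention, so randomised groups should differ on it only by chance. Every later value follows surgery. The STADI State and PSS values also follow the day-1 session, and the first cortisol value falls on the same day as that session.

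**Step 3: what is taken at T-4b?** Seven instruments: GEEE-Erwartung, SETS, Behandlungserfolg PR-OP, PHI, ASES-D, CARE and the warmth and competence scale. A data-collection session therefore already exists at the right moment.

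**Step 4: which parts of the key questions are affected?**

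- Question 1, expectations: covered by GEEE-Erwartung and SETS at T-4a and T-4b.
- Question 1, emotional states: no dedicated measure at T-4b.
- Question 4, self-efficacy: covered by ASES-D at T-4a and T-4b.
- Question 4, preoperative anxiety and stress: no dedicated measure at T-4b.
- Question 4, recovery and inflammation: covered by QoR-15 at T1 and by laboratory values at T-4a, T1, T3 and follow-up.

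**Step 5: could anything else fill the gap?** The PHI is scheduled at T-4a and T-4b, and the section on subjective outcome measures connects it with negative mood and distress. That use is tied to the early period after surgery, however, and Table 1 lists the PHI under Pain. The Setting section describes central assessments, including saliva samples and psychological questionnaires. It gives them no time point after the intervention and before surgery, and their stated purpose is cross-project analysis of predictors.

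**The case against.** A reader might infer that key questions 1 and 4 go unanswered as a whole. The documents do not support that: Step 4 shows that only one component of each is affected.

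A reader might also infer that emotional state is not measured at all before surgery once the intervention has been given. That too goes further than the documents allow. The PHI may carry some information on mood at T-4b, and its item content cannot be checked here. Table 1 is also not a full list of stress measures, because the central saliva samples are absent from it. Both points are fair and limit the finding. Neither closes the gap: the PHI is not presented as an anxiety or stress scale, and no suitable timing is stated for the central measures.

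One might fear that discharge anxiety will be reported as if it were preoperative. Nothing in the protocol plans this.

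An article condenses a fuller protocol, so silence in it proves little. The finding does not rest on silence, because Table 1 gives explicit time points for each measure and names T-4b where it is used.

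Finally, the primary objective and the sample size concern pain, and the listed secondary objectives do not name preoperative anxiety or stress. That stands, and it is why the point is not critical to the trial.

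**Conclusion.** The concern holds for the emotional-state component of key question 1 and the anxiety and stress component of key question 4. None of the three listed anxiety and stress measures has a value between the first session and surgery, so an intervention effect on preoperative anxiety or stress is not estimable from them, whatever the sample size. The PHI could offer at most a limited, indirect signal on mood or distress.

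Severity is moderate. Randomisation, the sample size and the primary pain analysis are unaffected.

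The conclusion assumes that Table 1 and its legend give the schedule as it will be run, and that the central assessments have no unstated collection between the first session and surgery.

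**What to change.** 1. Add STADI State to T-4b in Table 1 and compare the groups at T-4b, adjusting for the T-4a score.
2. For stress, either add one brief item at T-4b, or reword the clauses in key questions 1 and 4 to what is measured, namely postoperative anxiety and stress. Repeating PSS on the same day may be unsuitable if it asks about a longer period; this is an assumption, since its recall window is not given in the article.
3. If recruitment is too far advanced for a new measurement, rewording both clauses is the minimum.
4. Reconcile the timing of the first session. The strengths and limitations list puts it 2 days before surgery, whereas the intervention sections put it 4 days before. This does not alter the finding, because T-4a and T-4b are defined relative to the intervention, but it should be settled before a measure is attached to T-4b.

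The cost is a few minutes of patient time in an existing session, a change to Table 1 and a small amendment. Patients enrolled before the change will lack the value. A score from the same visit also shows the immediate reaction to the session rather than anxiety just before the operation, and the report should say so.
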